## Abstract

**Background:**

To evaluate the impact of a nurse navigation program on treatment adherence and resolution of hepatitis C infection in patients with severe mental disorder.

**Methods:**

An open, randomized, controlled trial with blinded outcome assessment. The intervention group will engage in a nurse navigation program designed by mental health nurses. The program involves active screening for patients with severe mental disorder. The patients and caregivers included in the program will receive information, training, support and guidance throughout the treatment and recovery process, which involves different healthcare professionals and units. The control group will receive the standard of care, which includes follow-up by a family physician, referral to the hepatologist, serological testing, new referral to the hepatologist, onset of treatment, and follow-up. Multidisciplinary care will be provided along a coordinated and seamless clinical pathway led by a nurse navigator.

The primary endpoints are total recovery (hepatitis C cure) and treatment adherence. Occurrence of symptoms of schizophrenia and health-related quality of life will be also recorded. Follow-up of patients will be performed three and six months after the administration of antiviral treatment.

The study was authorised by the Ethics Committee of Malaga in December 2021. Funding was approved in March 2021.

**Discussion:**

If this intervention is proven to be effective in improving treatment access and adherence, it will represent a step forward in addressing a chronic health issue that is 16 times more prevalent in the population with severe mental disease. Finally, this intervention may lead to the detection of undertreated HCV infection in this population of patients.

**Trial registration:**

This protocol has been registered in ClinicalTrials.gov with identifier code NCT04891445 on May 18, 2021.

## Introduction

Patients with severe mental disorder (SMD) (schizophrenia, bipolar disorder, schizoaffective disorder, major depression, and others) often experience poorer physical health than the general population. This may be explained by internal factors such as a sedentary lifestyle, poor diet and drug uses [1], which lead them to die, on average, 15–20 years earlier than the general population [2] Suicide rates in this population are also higher than in the general population [3].

This group is also at a higher risk of acquiring infectious diseases such as human immunodeficiency virus (HIV), hepatitis B (HBV), or hepatitis C (HCV), because they are more prone to engage in risk behaviors [4]. Attention needs to be paid on HCV, as this virus affects the liver, may cause a chronic disease, and may be transmitted to other people [5]. Moreover, Hepatitis C can be cured whereas Hepatitis B and HIV not.

The focus must also be placed on other healthcare issues, such as the lack of programs for the prevention, identification, and treatment of physical diseases in patients with SMD. A recent study in Ethiopia revealed that the prevalence of HCV infection (1.29%) is higher in patients with SMD, although it most frequently remains undiagnosed in this population (3 of 4) [6]. A high percentage of patients remain asymptomatic, the virus is associated with a higher risk of mortality, and patients with SMD frequently have treatment adherence problems [7]; therefore, the identification and proper management of the disease in SMD patients emerges as a highly relevant issue.

Some studies have shown how mental health nurses can adopt effective strategies to improve treatment adherence in patients with SMD [8, 9].

### Background

The scientific literature shows a well-established association between the presence of SMD, such as schizophrenia, and poor physical health, especially in young people [10]. As compared to the general population, life expectancy in women and men with schizophrenia is 15 and 20 years lower, respectively [2]. Around a fifth of premature deaths are associated with suicide and accidents, but most are caused by physical illnesses [11], including, among others, infectious diseases such as HIV and hepatitis [12, 13]. Moreover, the risk of death from infectious disease is almost ten times higher in people with psychosis and schizophrenia, than in the general population [14].

There is evidence that patients with SMD are at an increased risk for HIV, HBV and HCV infection, as compared to the general population [15]. Generally, patients with a psychiatric illness are less aware of the transmission of infectious diseases and protective measures [16]. Risk sexual behaviours, low quality of life, or long-term hospitalization may contribute to higher infection rates in this population [15].

The prevalence of HCV infection among psychiatric patients has not been clearly established in Spain. Previous studies report a prevalence of HCV 2 to 16 times higher in SMD patients than in the general population [17–19].

Although HCV remains virtually asymptomatic in many cases, patients with chronic infection experience a variety of symptoms that include depression, fatigue, and neurocognitive deficit, which affect their quality of life [20]. Likewise, patients with SMD are generally on treatment with neuroleptic or stabilizer drugs, which cause dejection, tiredness, and anhedonia. In addition, since SMD causes similar symptoms, this symptomatology will be rarely attributed to a physical health problem such as HCV [12].

As a result, HCV is frequently underdiagnosed and untreated in patients with SMD [6], mainly due to the side effects of interferon, the only treatment available until a few years ago. Several clinical studies reveal that immunomodulatory treatment with interferon causes numerous physical and mental side effects, mainly symptoms of depression, anxiety, psychosis, and other non-specific symptoms such as fatigue, irritability, sleep disturbances, psychomotor retardation, decreased libido, insomnia, and/or cognitive impairment [21–25]. These side effects cause this population to poorly tolerate HCV treatment.

In the recent years, Direct Acting Antiviral therapy with proven efficacy in the general population and very limited side effects have been approved [26]. These new treatments offer the possibility of re-evaluating the SMD population for administering the new treatments to the patients who did not tolerate previous treatments.

Protocols of mental health services do not usually include routine screening for HCV, which may remain underdiagnosed and untreated [6]. In addition, HCV infection may remain active in SMD patients [21].

Nielsen et al. proposed the implementation of programs for the management of mental and physical illnesses in SMD patients coordinated by a multidisciplinary team. The purpose of these programs is to optimize treatment outcomes and reduce dropout rates [27]. Most collaborative management programs have been endorsed by associations related to mental health, diabetes, and cardiology [28].

Several studies have analysed the effectiveness of mental health nurse-led interventions in addressing many of the challenges that standard management models are unable to address. Thus, forty clinical trials evaluating nurse-led multifaceted interventions have been identified in a scoping review; many of them were aimed at assessing treatment adherence and medication management in patients with psychosis and schizophrenia [29]. As educators and counsellors, mental health nurses address barriers to adherence by using shared decision-making techniques and tools, which engage and empower patients to actively participate in decisions about their treatment [30]. These skills could be applied to improve treatment adherence, medication management, and transitional care in different healthcare settings, such as in patients with psychosis and concomitant HCV infection. The therapeutic relationship that mental health nurses build with these patients and their families is also an advantage to improve both treatment adherence and user satisfaction [31, 32].

A qualitative study developed with patients with HCV who inject drugs revealed the difficulties to access to HCV treatment and highlighted the need for nurse navigator services that help patients navigate through a complex and fragmented healthcare system [33]. Moreover, some experiences with SMD patients with physical comorbidities treated in the US Medicaid system based on a nurse-navigator model have shown promising results in the seamless management of mental and physical health problems [34]. However, for these services to be effective, a solid and consistent approach is required, with well-defined limits and sufficient resolution capacity to bridge the various gaps that arise throughout the process [35]. Ryvicker's [36] behavioral-ecological conceptual framework for navigation addresses these two requirements. Thus, individual predisposing and limiting factors determine the degree to which a patient is able to navigate effectively through the health system (educational level, health literacy, communication skills, degree of self-efficacy, support from family caregivers, among others). The complex interaction between predisposing, facilitating, limiting factors and patient’s needs end up shaping their lifestyles and health practices. Provider factors such as continuity of care from different healthcare professionals, communication or respect and trust towards patients must also be considered. The confluence of these factors influences health outcomes, generating exacerbations of chronic diseases, hospitalizations, changes in functional status or poor quality of life. Finally, this model establishes ecological determinants such as the environment of health services, the social context of the person and the environment of people's lives. In the case of people with SMD both, predisposing and limiting behavioural factors, as well as ecological ones, acquire special relevance. Thus, when a SMD patient is diagnosed with a physical illness and treatment instructions are provided to them, patients will frequently not start the treatment immediately; instead, they will probably wait to discuss it first with their psychiatrist or mental health nurse or go home and not discuss the matter ever again. There are barriers during the consultation process, follow-up, and ongoing care, both associated to the health care providers and the patient that may lead to a poor compliance with a non-psychiatric treatment [37].

## The study

### Aims

The objective of this study is to compare the effectiveness of a nurse navigator program (NNP) developed by a team of mental health nurses, aimed at patients with HCV and SMD versus the usual standard of care. The variables to be assessed include HCV testing, treatment access and adherence, support for navigation throughout the healthcare system, and recovery from HCV.

The null hypothesis of this study is that there will be no differences in the HCV cure rate in SMD subjects who engage in the NNP versus those who receive the standard of care. Additionally, a second hypothesis would be that the intervention improves adherence to HCV treatment, expressed as a percentage based on the taken doses of prescribed treatment during the treatment period (from 0% to ≥ 100%).

### Design/ methods

A randomized clinical trial with blinded outcome assessment. This study has been registered in ClinicalTrials.gov (Identifier code: NCT04891445).

#### Population and sample

##### Population

Patients over 18 years of age included in the SMD program of the Mental Health Unit of the Regional University Hospital of Malaga will participate in the study. This Mental Health Unit is made up of several hospital and community units scattered around the city which will be prioritized to participate in the trial.

Patients for whom, for whatever reason, HCV treatment is contraindicated and patients with active SMD symptoms at the beginning of the study that might influence their ability to take part in the study will be excluded until stabilization. Those who do not give informed consent to participate will also be excluded from the study. In that case, they will receive the standard of care.

##### Sample

As far as we know, there are no comparative studies assessing adherence of SMD patients to HCV treatment. For this reason, adherence to lifelong treatments such as oral antidiabetics in patients with schizophrenia has been taken as a reference. Based on data from Kreyenbuhl et al. [38], in which differences in adherence of patients with schizophrenia reached 10%, with an alpha of 0.05, a beta of 20%, and raising the threshold of differences to 15% because, unlike oral antidiabetics, it is a temporary treatment, the needed sample would be 276, assuming that adherence will be 80% in the intervention group and 65% in the control group. This sample will be increased by 15% to cover losses. Additionally, we considered the adherence threshold obtained by Ho et al. in their pilot non-controlled study for patients with HCV and psychiatric disorders, [39] with the same estimation parameters, resulting in a similar sample size.

##### Endpoints and measures

The cure rate and adherence to treatment will be the primary endpoints. To assess cure, HCV viral load will be determined 8–12 weeks after the end of treatment. Patient adherence to treatment will be evaluated using the AIDS Clinical Trials Group method. By this method, patients are inquired about medications not taken in a period of four days prior to the interview: % adherence = (total galenic units prescribed for that period—total units not taken) / total galenic units prescribed for that period [40]. The cut point for this measure has been set to 95%, as the best threshold for a predictive positive virologic response in patients with HIV [41]. A record will also be kept of whether the patient needed to use a pillbox to ensure medication intake and/or required monitoring by the family or the mental health unit to guarantee the correct use of the treatment.

Secondary endpoints include sociodemographic and clinical data and data related to the healthcare process. Other variables in relation to the patient include changes in daily functioning as assessed using the Life Skill Profile (LSP) [42]; negative symptoms, measured on the Positive and Negative Syndrome Scale (PANSS) [43]; and changes in quality of life, measured with the Euroqol5D Health Questionnaire [44], all of them in their Spanish version (See Table 1). These questionnaires will be administered by an evaluator (psychologist or nurse) trained for it and blind to the experimental condition assigned to each patient.

**Table 1 Tab1:** Psychometric characteristics of the instruments included

Questionnaire	Domain (s)	Psychometric properties
**Life Skill Profile (LSP)** [42]	Self-care	Concurrent validity, this scale was compared with the social behaviour schedule SBS: 0.56 Interrater reliability *r* = 0.62, and internal consistency α = 0.82
	Interpersonal social behaviour	Concurrent validity, this scale was compared with the social behaviour schedule SBS: 0.54 Interrater reliability *r* = 0.69, and internal consistency α = 0.77
	Communication and social contact	Concurrent validity, this scale was compared with the social behaviour schedule SBS: 0.63 Interrater reliability *r* = 0.86, and internal consistency α = 0.86
	Non-personal social behaviour	Concurrent validity, this scale was compared with the social behaviour schedule SBS: 0.36 Interrater reliability *r* = 0.76, and internal consistency α = 0.78
	Autonomous life	Concurrent validity, this scale was compared with the social behaviour schedule SBS: 0.46 Interrater reliability *r* = 0.76, and internal consistency α = 0.80
**Positive and Negative Syndrome Scale (PANSS)** [43]	Positive symptoms	Concurrent validity, it was compared with the Andreasen positive scale, *r* = 0.70 Interrater reliability ICC = 0.72, and internal consistency α = 0.62
	Negative symptoms	Concurrent validity, it was compared with the Andreasen negative scale, *r* = 0. 81 Interrater reliability ICC = 0.80, and internal consistency α = 0.92
	General psychopathology	Interrater reliability ICC = 0.56, and internal consistency α = 0.55
**EuroQol 5D** [45]	Mobility Self-care Usual activities Pain/ Discomfort Anxiety/Depression	Concurrent validity, it was compared with the SF-6D, *r* = 0.73 [46] Construct validity it was evaluated in spanish population

Sociodemographic (age, sex) and socioeconomic data (job performance), where applicable, will be assessed using the Social Class Classification of the Spanish Society of Epidemiology (if the patient does not have a job, it will be recorded whether the patient is in a situation of retirement, unemployment, temporary disability, or job search). Consumption of drugs of abuse, regular psychiatric treatment, physical comorbidities, and their treatment, as well as type of diagnosis, time from disorder onset, availability of family support, and mental health hospital admissions in the last 12 months will also be recorded. Other data to be collected include adverse events or interactions reported by the patient or family caregiver and other important observations collected during evaluation and follow-up visits.

Regarding healthcare process indicators, the number of previously detected but untreated cases, detection rate after screening the SMD population, percentage of detected cases referred to the digestive service, and delay time until first consultation with the specialist will also be recorded. In addition, scheduled and unscheduled visits led by the monitoring team and number of calls made and received by this team will be recorded. Regarding hepatitis, case classification by genotype and treatment administered will also be recorded. In addition, the prevalence of undiagnosed HCV infection and diagnosed but untreated HCV infection in SMD patients will also be estimated. Finally, a comparison of daily life functioning, occurrence of symptoms, quality of life, and frequency of adverse events during active infection and once cured will be performed.

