#### Interventions

In this study, a navigation program led by mental health nurses and auxiliary nurse technicians from a mental health unit will be implemented.

The control group will receive the standard of care. Patients in this group will be directly referred to their family physician with a report showing a positive HCV and viral load test for prescription of the standard treatment established by the Andalusian Health System. Standard management involves referral to the gastroenterologist, with a significant delay. Generally, the gastroenterologist prescribes a series of tests to confirm diagnosis. These tests will be performed in other units, for which previous appointment is required. Once test results become available, the patient will have another consultation with the gastroenterologist, who will finally establish a diagnosis and prescribe the treatment. The prescribed drug will be dispensed at the hospital pharmacy once a month until the treatment is completed, and cure is confirmed. The last phase of the treatment involves a final visit with the gastroenterologist to confirm that the viral load has disappeared according to a laboratory test.

In the intervention group, patients will be accompanied throughout the evaluation and treatment process until they are fully cured. The details of the intervention are described following the template for intervention description and replication (TIDiER). Follow-up will include a simplification of the clinical pathway of treatment. This way, the mental health service refers the patient to a first visit with the gastroenterologist. To guarantee compliance, all patients will be accompanied to that appointment either by a competent available family caregiver or by a member of the NNP team.

In the first visit, the gastroenterologist will perform a liver ultrasound and determine the most appropriate treatment for each patient. In the same visit, the patient will receive the prescribed pharmacological treatment, which will be dispensed at the hospital pharmacy. Thus, the patient obtains a final diagnosis and his pharmacological treatment the same day following a single-step clinical pathway.

The mental health nurse team will subsequently arrange for the analysis of the genotype of the virus in the mental health service, if necessary.

The intervention is based on an *ad-hoc* decision algorithm developed by all the healthcare services involved (See Fig. 1).

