#### Data analysis

First, an exploratory data analysis will be performed to determine the distributions of the different variables and evaluate their normality using the Kolmogorov–Smirnov test, kurtosis analysis and skewness. Measures of central tendency and dispersion will be calculated, as well as percentage distributions. Subsequently, a bivariate analysis will be performed using the Chi-square test for comparison of qualitative variables, and Student's *t*-test for independent groups for quantitative variables. In case of non-parametric distribution, the Mann–Whitney *U* test will be performed.

In addition, repeated measures ANOVA will be used to determine intra-group progression of the different variables throughout the monitoring period, to evaluate the time effect.

Finally, a multivariate regression model will be constructed using Cox regression to evaluate the primary endpoints (cure and adherence), with follow-up periods as time adjusted for the variables found to have a significant association on bivariate analysis. The raw and adjusted hazard ratio for treatment failure and non-adherence will be estimated.

All the analyses will be performed by intention to treat (ITT) and by multiple imputation using the monotonic approach if missing data show a monotonic pattern; otherwise, the fully conditional specification will be used. Patients will be analysed in the group to which they will be initially allocated, regardless of whether they finally receive the randomized intervention.

All analyses will be done with estimation of 95% confidence intervals.

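### Delay to first specialist consultation exists only for patients who attend, and the plan's t-test/Mann–Whitney and imputation rules would bias it against navigation if the extra patients brought in attend later

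*Protocol article*

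**What the plan says.** Under Endpoints and measures, the article states: "Secondary endpoints include sociodemographic and clinical data and data related to the healthcare process". Among the process indicators listed there, "delay time until first consultation with the specialist will also be recorded".

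Data analysis names no test for this delay. Its general bivariate rule is "Student's *t*-test for independent groups for quantitative variables", followed by: "In case of non-parametric distribution, the Mann–Whitney *U* test will be performed". Cox regression is reserved for the primary endpoints, cure and adherence. On missing data it says: "All the analyses will be performed by intention to treat (ITT) and by multiple imputation". Nothing is said about patients for whom the consultation never takes place.

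Two other places bear on who attends. Background says that a patient with severe mental disorder who is told of a physical illness may wait to talk to the psychiatrist or mental health nurse, "or go home and not discuss the matter ever again". Interventions says that in the navigation arm "all patients will be accompanied to that appointment". Control patients are instead sent to the family physician, who refers them on, and that section describes the control referral as considerably delayed.

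**The concern.** A delay to a visit is a time to event. For a patient who is never seen it is not a missing measurement; it has no value within follow-up. Whether a patient attends is settled after randomisation, and accompaniment is meant to change it.

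Comparing attenders only therefore compares differently selected groups: controls who managed the pathway unaided, against nearly everyone in the navigation arm. Imputing within the planned framework does not solve this, because it assigns a consultation date to patients who had none and treats them as seen. By neither route does the comparison describe all randomised patients, which intention to treat promises.

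At stake is a secondary endpoint that bears on treatment access, one of the matters listed under Aims. If navigation brings in patients who would otherwise be lost, and they come late, their late visits count against it, while the control patients who never came count for nothing.

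**Working it through.** **The plan's own figure.** The only related figure is the sample size for adherence of 80% v 65%, two-sided alpha 0.05, power 80%:

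n per arm = [1.96·√(2·0.725·0.275) + 0.8416·√(0.80·0.20 + 0.65·0.35)]² / 0.15² = (1.238 + 0.524)² / 0.0225 ≈ 138.

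The total is 276, as stated. The 138 per arm is used below; 1:1 allocation is assumed because no ratio is given.

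**Assumed inputs.** None of these is in the article.
- Window W = 182 days.
- In both arms 60% would attend unaided. The median delay is 60 days with navigation and 60k days in control.
- Navigation brings in a further 35% at a median of 110 days.
- Delays are log-normal with log-SD s = 0.4.

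**Formulas.** For a group with median m:
- probability of being seen by day 182: P = Φ(ln(W/m)/s)
- mean delay among those seen: m·exp(s²/2)·Φ(ln(W/m)/s − s)/P
- restricted mean time without a consultation, per arm: seen × mean among seen + (1 − seen) × 182

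**Navigation arm.** Unaided patients: P = 0.997, mean 64.6 days. Extra patients: P = 0.896, mean 107.0 days. Seen: 0.60·0.997 + 0.35·0.896 = 91.2%. Mean among those seen: 79.2 days. Restricted mean: 0.912·79.2 + 0.088·182 = 88.3 days.

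**Control arm, by k:**

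| k | Seen | Mean, attenders | Navigation minus control, attenders | Restricted mean | Gain with navigation, all randomised |
|---|---|---|---|---|---|
| 1 | 59.8% | 64.6 | +14.6 | 111.8 | 23.5 |
| 1.25 | 59.2% | 79.5 | −0.3 | 121.3 | 33 |
| 1.5 | 57.7% | 92.7 | −13.4 | 130.5 | 42 |
| 2 | 51.1% | 112.9 | −33.7 | 146.7 | 58 |

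The distortion can be isolated. Unaided patients in the navigation arm wait 64.6 days on average, but that arm's attenders average 79.2. The difference, 14.6 days, comes only from adding later attenders, and it is the same in every row. The like-for-like shortening is 0, 15, 28 and 48 days for the four values of k; the attenders-only comparison shows −15, 0, 13 and 34.

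**Test results by simulation.**
- k = 1: Mann–Whitney is significant in the wrong direction in about 83% of trials. Log-rank on all randomised patients favours navigation in about 99%.
- k = 1.25: wrong direction in under 1%.
- k = 1.5: right direction in about 87%.
- k = 2: right direction in 100%.
- k = 1 with other log-SDs: the 83% ranges from about 97% at 0.3 to 60% at 0.5 and 44% at 0.6.

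**If the extra patients attend as early as the rest** (median 60 days, k = 1), the attenders' difference is about 0, with about 2% significant in the wrong direction. The comparison then misses the access gain but does not reverse it: 111.8 − (0.947·64.6 + 0.053·182) = 111.8 − 70.8 = 41 days.

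**A second set of assumptions.** Here 60% of patients are easy and 40% hard to reach; attendance with navigation is 98% and 90%, in control 90% and 10%; mean delays are 30 and 80 days; the window is 180 days.
- Equal delays for like patients: attenders' means are 33 days in control and 48 with navigation. This is significant in the wrong direction in 96% of trials by t-test, and in 96% after imputation within arm. The restricted means are 95 and 56 days, in favour of navigation.
- Control delay 1.5 times as long: 48 v 48.
- Control delay 2 times as long: 62 v 48, against restricted means of 113 v 56.
- If 40% or 70% of hard-to-reach controls attend, the reversal is gone at about 1.25 or 1.1 times.

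**The case against.** The strongest reply is that no test is assigned to this variable. The article says only that the delay is recorded, among other process indicators, and a fuller analysis plan may define a censored analysis. It stands that the link is an inference from the general rule. But the rule is stated for quantitative variables without exception, imputation is stated for all analyses, and survival methods are named only for the two primary endpoints. Read as written, the rule does not fit this variable.

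A reader might infer that the trial will show navigation as slower. The documents do not support that. Reversal needs similar delays for like patients in both arms and extra navigated patients who come late. Interventions describes a marked delay in control and a shortened pathway under navigation, and nothing says that accompanied patients attend late. In the scenarios above reversal disappears once the control delay is about 1.1 to 1.5 times as long.

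A reader might also infer that many patients are expected never to attend, or that access will be judged on this delay alone. Background gives no rate and describes waiting to consult the mental health team as an alternative. Endpoints and measures also records the percentage of detected cases referred to the digestive service and the treatment administered.

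Finally, the attenders' difference and the restricted-mean gain are different quantities, so a gap between them is not all bias. That is fair; the 14.6-day composition effect is the part that is bias under the stated assumptions.

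**Conclusion.** The concern holds in a limited form. The stated rule would compare this delay among attenders or after imputation, and the design makes unequal attendance likely. The result is biased against navigation when the additional patients attend later than the others. The direction of the bias follows from that condition. Its size rests wholly on assumed attendance rates, delays and spread: about 15 days in the main scenario, with an apparent effect that is reversed, absent or understated as the control delay goes from 1 to 2 times the navigation delay. Given the article's own description of the control pathway, a masked or understated benefit is the likelier error. The point concerns one secondary process endpoint. Cure, adherence and the sample size of 276 are untouched.

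**What to change.** In Data analysis, exempt this variable from the t-test/Mann–Whitney rule and from multiple imputation. Define it as time from randomisation to first specialist consultation and analyse it in all randomised patients by Kaplan–Meier with a log-rank test, a Cox hazard ratio or restricted mean time.

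Censor patients who are never seen at a fixed time from randomisation, or at last contact if earlier. The time should run from randomisation because the six-month assessment under Monitoring is counted from the start of treatment, a date that a never-seen patient does not have. Report the proportion seen by a fixed day in each arm beside the time-to-event result.

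The cost is analysis wording only. The delay is already to be recorded, and no visit, sample size or primary analysis changes.
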